### Drug preparation and administration

Good Manufacturing Practice (GMP) quality LSD Hemitartrate Active Pharmaceutical Ingredient (Psygen Ltd, Calgary, Canada) will be formulated to GMP by Biocell Corp (Auckland, New Zealand) to produce MB-22001—the investigational medicinal product (IMP) to be used in this trial. The Contract Manufacturer will receive a MedSafe Manufacturing license for the IMP prior to manufacturing the first clinical trial batch. Investigational products will be labelled consistent with legal requirements. All participants will be offered a lockbox to securely keep the IMP in at home—and to prevent accidental ingestion by minors. MB-22001 is a liquid formulation that participants can self-administer sublingually.

### Titration protocol

To ensure participant acceptability of dosage, this study will utilise a titration protocol. LSD is known to have stimulant-like effects, even at low doses, which can result in feelings of uneasiness or overstimulation [39]. This effect can vary from person to person. Flexibility in dosage ensures participants will be receiving an appropriate dose, reducing the likelihood of negative side effects that would be counter-productive to the purpose of the trial. Based on findings from the MDLSD study, the starting dose will be 8 µg, increasing or decreasing at a rate of 1 or 2 μg per dose. This is lower than the dose in the MDLSD study (10 µg). The maximum dose given to participants will be 20 μg. The decision to increase the dose will be based on participant feedback and psychometrics, such as the subjective drug effects questionnaire. The most appropriate dose for a participant will be one in which they may feel subtle effects of the LSD, but not to the extent that effects are negative, overstimulating, or consciousness altering. Participants will be informed that if they experience any disturbance of daily functioning they should decrease the dose for the next dosing.

Participants will use a 5-point Likert scale in the dose day questionnaires to rate the tolerability of the previous dose. Doses will then be decreased in 2 or 1 μg increments if the last dose had any tolerability issues (i.e. was rated as ‘too much’) or increased by 2 or 1 μg increments if they feel no effects at all and rated the dose as inadequate.

To reduce the likelihood that titration procedures will impact blinding, participants will be informed that it is not uncommon for people to increase their dosage to 20 μg and not feel anything. Titration procedures will be aided by an in-app questionnaire, asking for subjective experience of their last dose, with oversight from the study team.

### Relevant concomitant care and post-trial care

Participants will continue to receive standard care from their GP or wider medical team for the duration of the trial. Long-term harm to participants is considered highly unlikely; however, participants can apply for compensation for any injury sustained during the trial under the Auckland University insurance policy.

### Sample size

Given the primary aim of this study to establish the feasibility, acceptability, and safety of PA-MCP for future investigation in a fully powered clinical trial, this study is not powered or intended to determine statistical significance [74]. With the proposed sample of 40 participants, we are able to estimate a compliance rate of 80% to within a 95% CI of within ± 12%. This sample size will provide sufficient data to assess feasibility, acceptability, and safety metrics based on a recent study investigating psychedelic-assisted psychotherapy in cancer patients (*N* = 29; Ross et al., 2016) and previous MCP studies where 66–71% of participants completed all 7 psychotherapy sessions [21, 22].

### Statistical analyses

Baseline measures will be presented for each treatment group using summary statistics, with frequencies and percentages for categorical variables and means with appropriate measure of spread for continuous variables. Data on quantitative primary outcome measures for feasibility, acceptability, and safety for Māori and non-Māori participants including recruitment rates, attrition, adherence to medication and MCP, adverse effects, MCP treatment fidelity, and feasibility of outcome data collection will also be presented using descriptive statistics.

Changes in secondary outcome measures over the study period will be assessed using generalised linear mixed models (GLMMs) with main effects of treatment (PA-MCP versus Placebo-MCP) and time (T0–T9), treatment-by-time interactions, and subject-level random effects to model longitudinal trajectories whilst accounting for correlations between repeated measures within subjects.

Qualitative interviews will be analysed using thematic analysis, a systematic process for identifying patterns in qualitative data [75]. Interviews will be transcribed and read in detail to gain familiarity with the data. The transcripts will be coded to identify emergent features; these codes will then be reviewed, refined, and organised to produce themes. Though this process will be reflexive and iterative, themes will be considered in relation to our primary outcomes, as well as those relating to experience, expectations/knowledge, and psychological wellbeing. Finally, these themes will be considered in context of broader trial findings and the wider literature.

### Adverse event reporting and harms

An adverse event (AE) is any untoward medical occurrence (e.g. any unfavourable and unintended sign [including abnormal laboratory findings], symptom, or disease) in a participant after being confirmed into the trial until the night of the last study visit. Therefore, an AE may or may not be temporally or causally associated with the use of the investigational medicinal product. Any intentional misuse and abuse of the product and consequences thereof are also considered an adverse event irrespective if a clinical event has occurred.

AEs include any medical occurrence in a participant, including any abnormal sign (e.g. abnormal physical exam or laboratory finding), symptom, or disease, temporally associated with the participant’s involvement in the research, whether or not considered related to participation in the research. This definition includes concurrent illnesses or injuries and exacerbation of pre-existing conditions. They do not include anticipated day-to-day fluctuations of pre-existing disease(s) or condition(s) present or detected at the start of the study that do not worsen.

All AEs occurring on-site will be recorded by study staff in the CRF, whether or not attributed to trial medication. Any adverse effects when participants are off-site on dose days only will be recorded via participants’ daily report form. AEs recorded in the daily report form will be reviewed daily.

Events judged to be Serious Adverse Events will be reported to MedSafe as per Sect. 6 of the MedSafe reporting guidelines described in the Regulation of Therapeutic Products in New Zealand Part 11: Clinical trials – regulatory approval and good clinical practice requirements. These are submitted via the HDEC website (https://nz.forms.ethicalreviewmanager.com) as soon as is practical. In addition, SAEs will be reported in real-time to the HRC Data Monitoring Committee.

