**Methods:**

Participants with advanced-stage cancer and symptoms of anxiety and/or depression (*N* = 40; 20 Māori, 20 non-Māori) will be randomised under double-blind conditions to receive 7 sessions of MCP alongside 13 doses of either an LSD microdose (4–20 µg) (PA–MCP) or inactive placebo (placebo-MCP). The feasibility, acceptability, and safety of this intervention and physiological and psychological measures will be recorded at baseline, at each session of MCP, and at a 1-month and 6-month follow-up.

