Outcome domain	Measure	Definition
Feasibility	Adherence to medication regimen	Compliance with study treatment (at minimum 80% of doses taken indicates feasibility, i.e. 11 out of 13 doses taken)
	Attendance at MCP session	Percentage of participants attending 4 out of 7 sessions
	MCP treatment fidelity	Rating on the Memorial Sloan Kettering Fidelity Rating Scale. A 5-item yes/no indicating presence of content, a 5-item 3-point Likert scale measuring coverage, and a final 5-point Likert scale assessing overall focus on meaning/purpose
	Participant recruitment	Percentage of consented participants randomised (70% or greater indicates feasibility)
	Attrition	Number of dropouts following randomisation (30% or less indicates feasibility)
Acceptability	Qualitative interviews	Semi-structured qualitative interviews at baseline and at 1 month following treatment completion (T8) (participant and support person) and will address expectations and the acceptability of study procedures
	Completeness of data	Percentage of complete data
Safety	Vital signs	Monitoring of vital signs including heart rate, blood pressure, and body temp at 0, 30, 120, 240, and 360 min post-administration at T1. Also measured at 0- and 45-min post-administration, for T2–T7. Serotonin syndrome checks on every in-clinic day T1–T7
	Palliative Care Outcomes Collaborative Symptom Assessment Scale (PCOC-SAS)	Nine symptom items on an 11-point scale of distress, rated from ‘absent’ to ‘severe’
	Adverse events	Participants are asked on dosing days to report any ‘unpleasant health effects’ and to rate them as mild, moderate, or severe
	ECG data	ECG data will be reviewed by a study physician, noting where reference ranges are exceeded

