### Outcomes

Primary and secondary outcome measures are outlined in Tables 4 and 5. Feasibility measures include adherence to medication regimen, attendance at MCP sessions, MCP treatment fidelity, and participant recruitment and attrition rates; the feasibility targets (detailed below) are based on previous research [21, 22]. Acceptability will be assessed using open-ended questions (T0–T9) and semi-structured qualitative interviews at baseline and at the one and 6-month follow-ups. Furthermore, the completeness of data will also be used to indicate the acceptability of completing study measures. Safety assessments include physiological data (HR, BP, body temperature), weekly symptom reporting, adverse event reporting, and ECG taken on the last study visit.

**Table 5 Tab5:** Secondary measures

Outcome domain	Measure	Scale
Sense of meaning	Personal Meaning Index of the Life Attitude Profile – Revised (LAP-R) [56]	16 items, 7-point Likert scale from 1 (strongly agree) to 7 (strongly disagree). Scores are summed
Quality of life	Functional Assessment of Chronic Illness Therapy – General (FACT-G) [57]	27 items, 5-point Likert scale from 0 (not at all) to 4 (extremely). Four subscales, summed
Spiritual well-being	Functional Assessment of Chronic Illness Therapy – Spiritual Well-being 12-item scale (FACIT-SP-12) [58]	12 items, 5-point Likert scale from 0 (not at all) to 4 (very much). Scores are summed
Sense of connectedness	Watts Connectedness Scale [59]	19 items, rated on VAS (0–100), anchors: ‘Not at all’ and ‘Entirely’. Three subscales, reported as mean scores and subscale means
Anxiety and depression	Depression, Anxiety and Stress Scale (DASS-21) [60]	21 items, 5-point Likert scale, from 0 (never) to 4 (almost always). Three subscales, reported as summed scores (each subscale sum multiplied by two)
	Hospital Anxiety and Depression Scale (HADS) [61]	14 items, 5-point Likert scale (0–4). Two subscales, reported as summed scores
Te Whare Tapa Wha Mental Health outcomes	Hua Oranga [62]	14 items, 5-point Likert Scale (1–5). Four subscales, reported as subscale or total questionnaire summed scores
Demoralisation	Demoralization Scale [63]	24 items, 5-point Likert scale, ranging from 0 (never) to 4 (all the time). Five subscales, reported as summed scores
Attitudes towards death	Schedule of Attitudes towards Hastened Death (SAHD) [64]	20 items, scored 0 (false) or 1 (true), reported as a total sum

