### Randomisation, masking, and code-breaking

A biostatistician ([name]) will perform randomisation of the allocation of participants to the interventions. The biostatistician will generate a randomisation code list, and participants will be randomised in randomly permuted blocks with stratification used to give separate lists for Māori and non-Māori. The active and placebo interventions will be matched in appearance. Only the biostatistician and pharmacists involved in the study will be unblinded to study group allocation. These persons will not interact with study participants and will not be present during any drug administration sessions. To ensure allocation concealment when a participant enters the trial, they will then be allocated by a blinded investigator to the first available code on the randomisation sequence list. Both participants and Investigators will be kept blinded until the End of Trial. The Start of Trial is the date of the first screening visit for the first potential participant. The End of Trial is the date of the last 1-month follow-up interview of the last participant. Each participant is considered an active trial participant from the first screening visit until 1-month follow-up unless otherwise withdrawn. In case of emergency, study pharmacists will also keep an electronic spreadsheet of allocations so that de-blinding can be performed rapidly.

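### Structured adverse-event questioning stops at the last dose, although the adverse-event period runs to an undated last study visit and the abstract places safety recording at 1 and 6 months

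*Protocol article*

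**What the plan says.** Five places in the protocol article bear on when safety observation ends.

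- **Adverse event reporting and harms.** An adverse event is an untoward medical occurrence "in a participant after being confirmed into the trial until the night of the last study visit". For capture, the same section says: "All AEs occurring on-site will be recorded by study staff in the CRF, whether or not attributed to trial medication". Away from the clinic the rule is narrower: "Any adverse effects when participants are off-site on dose days only will be recorded via" the participant's report form.
- **Table 4, Safety rows.** The adverse-event measure reads "Participants are asked on dosing days to report any" unpleasant effects on health, each rated mild, moderate or severe. The vital-signs row also covers T1 to T7 only, and adds "Serotonin syndrome checks on every in-clinic day T1–T7".
- **Outcomes.** The safety list ends with "adverse event reporting, and ECG taken on the last study visit". This is the same visit label, again without a date.
- **Abstract, Methods.** Feasibility, acceptability, safety and the physiological and psychological measures "will be recorded at baseline, at each session of MCP, and at a 1-month and 6-month follow-up".
- **Randomisation, masking, and code-breaking.** "Each participant is considered an active trial participant from the first screening visit until 1-month follow-up unless otherwise withdrawn". The End of Trial is the last participant's 1-month interview. Six-month assessments are nevertheless planned in the abstract, in Outcomes and in the Discussion.

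**The concern.** Safety is one of the three primary objectives. The Background notes that microdosing side effects are reported as acute rather than lasting, and that such observational results need checking in more rigorous trials. This trial is placed to do that only if it collects adverse events in the same graded form after dosing has stopped.

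As described, it does not. The definition may let an event count until some later visit, but the described procedure for asking about and grading events stops with the last dose. A table of adverse events by arm would then hold on-treatment events plus whatever reached the study team by other routes.

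The end of the period matters for the count as well. The definition includes concurrent illness and worsening of existing conditions. In stage IV disease such events will continue to occur, so the total depends on the date at which counting stops.

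**Working it through.** **The plan's own figures.** The listed dosing days number 13 and the last is day 43. 6 × 7 + 1 = 43, which agrees with 6 weeks and 1 day. With all seven break weeks, 43 + 7 × 7 = 92, and 13 × 7 + 1 = 92, which agrees with the stated maximum of 13 weeks and 1 day. Both figures reproduce.

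**Candidate ends of the period.** The last study visit could be the day-43 clinic visit (T7), the 1-month contact (T8) or the 6-month contact. I take 1 month as 30 days and 6 months as 183 days. Both are counted from the end of treatment; the article anchors only T8 that way, so this is an assumption for the 6-month contact. Day 1 stands in for confirmation into the trial. The true start is somewhat earlier and adds the same unknown number of days to every period.

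| End of period | No break weeks | Ratio | All seven break weeks | Ratio |
|---|---|---|---|---|
| Last dose | 43 | 1.0 | 92 | 1.0 |
| 1-month follow-up | 43 + 30 = 73 | 73/43 = 1.7 | 92 + 30 = 122 | 122/92 = 1.3 |
| 6-month follow-up | 43 + 183 = 226 | 226/43 = 5.3 | 92 + 183 = 275 | 275/92 = 3.0 |

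**How much of each period has no structured enquiry after the last dose.** To 1 month: 30/73 = 41% without breaks and 30/122 = 25% with all seven. To 6 months: 183/226 = 81% and 183/275 = 67%. If the last study visit is T7, the period itself closes on the night dose 13 is taken.

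**Routes that remain open after the last dose, set against what is needed.**

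| Route | Where | Graded adverse-event count described? |
|---|---|---|
| Dose-day question | Table 4 | Yes, but it ends with dose 13 |
| Off-site report form | Adverse event reporting and harms | Dose days only |
| On-site events recorded by staff | Adverse event reporting and harms | No end date, no list of visits and no severity rating stated |
| Serious events reported to the regulator and the monitoring committee | Adverse event reporting and harms | Serious events only |
| Notification of medical conditions and procedures within 48 h | Table 1 | Volunteered and ungraded |
| Health-status changes at each visit | Study design | Not described as adverse-event grading |
| Follow-up interviews asking about negative effects | Discussion; Statistical analyses | Analysed by theme |
| Open-ended questions, T0 to T9 | Outcomes | An acceptability measure |
| Psychometric scales at 1 and 6 months | Outcomes | Secondary scores, not adverse events |

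No row gives a structured, severity-rated count after the last dose.

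**The case against.** Only the adverse-event section sets an adverse-event period. Table 4 says how participants are asked, the randomisation section defines active status, and the abstract sentence lists several domains together without saying that each is measured every time. A reader might infer that the plan formally fixes three different ends for safety follow-up. It does not. Day 43 is where the described questioning stops in practice, and the last study visit may coincide with one of the other points.

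The schedule figure is not shown and the article condenses a longer protocol. Either may date the last visit or place an adverse-event review at T8. That limits the charge that the visit is undated. It does not reconcile the abstract's follow-up wording with the dose-day-only wording, or with an end of active participation at 1 month.

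A reader might also infer that the trial could declare no lasting harm without having looked. That is too strong. The interviews ask about negative effects, participants undertake to report medical conditions, health-status changes are reported at visits, and serious events are reported without a dosing-day limit. What stands is narrower: these routes are not described as yielding graded counts by arm.

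Lastly, any period applies equally to both randomised arms and the safety analysis is descriptive, so no bias between arms is shown.

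**Conclusion.** The point holds in limited form. The article counts adverse events to a visit that its text does not date, describes graded enquiry only up to the last dose, places safety recording at 1 and 6 months, and ends active participation at 1 month. The primary adverse-event data, as described, support statements about effects during dosing. They do not support a quantitative statement on persisting or delayed effects.

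The candidate periods differ by up to 5.3-fold without break weeks and 3.0-fold with all seven. These ratios rest on 30- and 183-day months counted from the end of treatment. They compare lengths of observation and are not forecasts of event counts, because the documents give no adverse-event rate.

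A projection of deaths under each period would be a tempting measure of size. The documents give no survival figure beyond an entry prognosis of at least 6 months, and ascertainment of death does not depend on a dosing-day question, so such a projection would not measure this gap.

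The change is worth making because safety is a primary objective and the remedy is small.

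**What to change.** 1. Give the last study visit a visit number, and state one period for adverse and serious adverse events. Keep the existing start at confirmation into the trial and end at the 1-month follow-up (T8). The documents do not say which end is intended; T8 is proposed because it matches the stated end of active participation.
2. At T8, ask the existing Table 4 adverse-event question with its mild, moderate or severe rating, covering the time since the participant's last dose.
3. Report on-treatment and post-treatment events separately, by arm.
4. Report events learned of at 6 months descriptively, outside that count.
5. Align the abstract, Table 4, Outcomes, the randomisation section and the adverse-event section with this period, including which visit the ECG belongs to.

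The cost is protocol wording and one existing question at an existing contact. More disease-related events will be counted in both arms; reporting the two periods separately keeps that visible.

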### Safety and tolerability

Despite the good safety profile of LSD [40], surveys of psychedelic microdosers often report mild side effects. These include psychological effects, such as racing thoughts or increased anxiety, and physiological effects, such as headaches or sleep problems [41]. However, not everyone who microdoses report side effects. Among an online sample of psychedelic microdosers, 30% reported no side effects [41], and in another online study of 1116 microdosers, only 20% of the sample reported adverse effects [42]. Furthermore, these effects are reported to be acute rather than persisting long term. However, results from observational research need to be verified in more scientifically rigorous trials, as variability in microdosing practices, dosages, quality of substances, and measurement time points limit the validity of the results.

To date, several laboratory-based randomised controlled trials have explored the effects and safety of LSD microdosing. Excluding the MDLSD study [39] (see below), five studies with unique samples have been conducted. Safety data collected in these trials consisted primarily of blood pressure, heart rate, and basal body temperature. The first tested three doses of LSD tartrate (6.5, 13, 26 μg) compared to placebo in a within-subjects design [43]. Participants in this study reported dose-dependent increases on the 5D-ASC, a scale used to measure consciousness-altering effects. An increase in blood pressure, but not body temperature or heart rate, was observed at the 13 and 26 μg doses, an effect observed in other research [38, 44]. No other safety data or adverse events were reported. In another study, the highest dose produced modest subjective effects, including increased ratings of ‘feeling a drug effect’, significant peak change scores on the Profile of Mood States Vigor subscale, and ratings of stimulant-like and LSD-like effects [45]. However, no effects on any cardiovascular measures were reported.

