Personality	Big Five Inventory (BFI-2-XS) [65]	15 items, 5-point Likert scale, ranging from 1 (disagree strongly) to 5 (agree strongly). Five subscales, reported as summed scores
Therapeutic alliance	Working Alliance Inventory Short Form (WAI-SF) [66]	12 items, 5-point Likert scale, ranging from 1 (seldom) to 5 (always). Three subscales, reported as summed scores
Altered states of consciousness	5-Dimensional Altered States of Consciousness Rating Scale (5D-ASC) [67]	94 items, with 5 scales and 11 subscales reported as % of the maximum score
Personality: absorption	Modified Tellegen Absorption Scale (MODTAS) [68]	34 items rated on a 5-point scale (0–4) reported as the sum of scores (0–136)
Treatment expectancy	Treatment Expectancy Questionnaire [69]	15 items rated on an 11-point Likert scale
Pain	Brief Pain Inventory – Short Form (BPI-SF) [70]	4 severity items and 7 interference items, rated on an 11-point Likert scale, ranging from 0 (no pain/does not interfere) to 10 (pain as bad as you can imagine/completely interferes), the two subscales are reported as means
Measurement of blinding	Dose Day Questionnaire	Single-item measure (placebo, LSD, don’t know)
Subjective drug effects	Drug Effects Visual Analogue Scale [39]	12 items, rated on VAS (0–100), reported individually and as mean score
Caregiver stress – support person only	Kingston Caregiver Stress Scale [71]	10 items, rated on 5-point Likert scale, reported as the sum of scores (10–50)
Closeness to others – support person only	Inclusion of Other in Self [72]	Single-item measure, between 1 and 7

The schedule of assessments is detailed in Fig. 1. Key time points for psychometrics are days 1, 22, and 43, as well as the 1- and 6-month follow-ups (see Fig. 1). In addition to psychometrics, vital signs and serotonin syndrome checks will be conducted at every in-clinic visit. Participants will also record adherence to dosing, subjective drug effects, measurement of blinding, and any adverse events on home dosing days.

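### Adverse events are defined continuously but off-site events are recorded on dose days only, so events on 30 of 43 treatment days have no stated route into the AE record; vital signs beyond 45 minutes exist only for the 8 µg starting dose

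*Protocol article*

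**What the plan says.** Objectives names safety among the primary objectives, and Table 4 lists adverse events among the primary safety measures.

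- **Definition.** Adverse event reporting and harms counts any untoward occurrence "in a participant after being confirmed into the trial until the night of the last study visit". No link in time or cause to the study drug is needed. Concurrent illness and worsening of existing conditions are included.
- **Collection.** The same section has staff record on-site events in the CRF, and then says: "Any adverse effects when participants are off-site on dose days only will be recorded via" the participant's daily report form. Table 4 agrees: "Participants are asked on dosing days to report any ‘unpleasant health effects’ and to rate them as mild, moderate, or severe". Outcomes has participants record "any adverse events on home dosing days". Data collection and management describes the CRF content as adverse events at the study site.
- **Vital signs.** Table 4 lists readings at 0, 30, 120, 240 and 360 minutes at T1. For later visits it says: "Also measured at 0- and 45-min post-administration, for T2–T7". None are listed for home doses.
- **Dose.** Titration protocol starts everyone at 8 µg, allows steps of 1 or 2 µg per dose and sets a maximum of 20 µg. Of one earlier study, Safety and tolerability reports: "An increase in blood pressure, but not body temperature or heart rate, was observed at the 13 and 26" µg doses.

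**The concern.** The definition and the collection rule describe different sets of events. An event that starts at home on a non-dose day is an AE by definition, but no stated route takes it into the AE record. The word limiting collection to dose days is an explicit restriction and not a detail lost in condensing the protocol, and three other places in the article agree with it.

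The uncovered days are not obviously quiet ones. The article itself names anxiety and sleep problems as expected effects and sets a 2 pm dosing limit to protect sleep, so a disturbed night may first be noticed the day after a dose. Break weeks are taken when a participant is unwell or in cancer treatment. They contain no dosing and hence no dose-day form. At stake is the AE incidence that a larger trial would be planned on.

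The vital-sign point is separate. The long series is taken only at the lowest point of any upward titration, so a statement that vital signs did not change could be read as covering doses at which the later readings were never taken.

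**Working it through.** **1. The plan's own counts.** Study design lists dosing on days 1, 4, 8, 11, 15, 18, 22, 25, 29, 32, 35, 39 and 43. That is 13 days, 7 in clinic and 6 at home, matching the stated 13 doses over 43 days. Seven break weeks give 43 + 7 × 7 = 92 days, matching the stated 13 weeks and 1 day. (The MCP session list has day 36 where the dosing list has day 35; the counts do not change.)

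**2. Days with AE recording.** All seven treatment clinic days are also dose days, so the on-site and off-site routes together cover the same 13 days.

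| Treatment period | Covered | Not covered |
|---|---|---|
| No break weeks, 43 days | 13/43 = 30% | 30/43 = 70% |
| Seven break weeks, 92 days | 13/92 = 14% | 79/92 = 86% |

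There are no dose days after day 43. Randomisation, masking, and code-breaking keeps a participant active until the 1-month follow-up. If that is the last study visit meant in the AE definition, the off-site time between day 43 and that visit is uncovered too.

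**3. Could other routes fill the gap?** Study design has participants report changes in health status at each visit and on each dose-day questionnaire. PCOC-SAS scores nine fixed symptoms and is listed as a separate measure. Table 1 asks participants to tell investigators of medical conditions and procedures within 48 hours. SAE reporting is not limited to dose days. None of these is stated to enter the AE record.

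**4. Size of the under-count.** The article gives no event timing, so this is an illustration. Assume 20 active participants, true incidence p with at most one event each, a share f of events falling on a recorded day, and no later recall. Then P(at least one recorded) = 1 − (1 − p·f)^20.

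| Share f on recorded days | p = 5% | p = 10% | p = 20% |
|---|---|---|---|
| 1 (all recorded) | 64% | 88% | 99% |
| 0.8 | 56% | 81% | 97% |
| 0.5 | 40% | 64% | 88% |
| 13/43 (even over 43 days) | 26% | 46% | 71% |
| 13/92 (even over 92 days) | 13% | 25% | 44% |

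At p = 10% and f = 13/43, for example, p·f = 0.0302 and 1 − 0.9698^20 = 0.46. The loss is small if events cluster on dose days and large if they do not.

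**5. Vital signs against dose.** At the fastest permitted rise (2 µg per dose) the path is 8, 10, 12, 14, 16, 18, 20. Dose 4 (day 11, at home) is the first above 13 µg, and dose 7 (day 22, T4) is the first at 20 µg. At 1 µg per dose, 13 µg comes at dose 6 (day 18) and 20 µg at dose 13 (day 43). One dose, always 8 µg in the active arm, is followed to 360 minutes. Six clinic doses are followed to 45 minutes, and six home doses have no readings listed. Measured against the protocol's own 360-minute window, that is (360 + 6 × 45)/(13 × 360) = 630/4,680 = 13.5%. No raised dose is followed past 45 minutes.

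**The case against.** Calendar days are not exposure. Every one of the 13 dose days has AE reporting, break weeks have no dosing, and the article describes microdosing side effects as acute (while adding that this needs verification). This stands: a reader might infer that the safety outcome misses most of the drug exposure, and the documents do not support that. What is missed is most calendar days of the AE window.

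The trial has other safety information: the routes in step 3, the 1-month interviews that ask about negative effects, and DASS-21 at the key time points. The dose-day form may also look back in practice, since its tolerability item already rates the previous dose, and the full form is not shown. This is why the under-count cannot be called certain. It does not remove the mismatch, because the written rule excludes non-dose days off site.

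The trial is descriptive and the rule is the same in both blinded arms. That protects the comparison only if events fall on non-dose days equally often in both arms; a next-day drug effect would be lost from the active arm alone.

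On vital signs, a reader might infer that monitoring is cut short when a dose is raised. It is not: the schedule is set by visit for everyone. Nor does the article show that the trial's doses raise blood pressure. Safety and tolerability also cites a study with no cardiovascular effects, an older-volunteer study at up to 20 µg found no clinically significant abnormality, and the MDLSD study found no change. The 13 and 26 µg doses are given as LSD tartrate, and the article does not say whether its own doses are salt or base, so 13 µg is only an approximate marker. The fastest titration path is also a limiting case, since increases are for participants who feel no effect.

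**Conclusion.** The point holds in a limited form. The AE definition is continuous, while the stated collection rule leaves 30 of 43 treatment days (70%), up to 79 of 92 (86%), without a stated route into the AE record. The interval from day 43 to the 1-month visit is added if that visit closes the AE window. AE incidence as defined can therefore be under-counted. The amount is unknown and depends on event timing and on how far the other routes are used in practice.

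The vital-sign finding is a limit on what may be concluded, not evidence of harm: no reading after 45 minutes will exist for any dose above 8 µg. The cited blood-pressure evidence is mixed, which is a reason to state that limit plainly and not to assume a result in either direction.

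**What to change.** **Adverse events.** Remove the restriction to dose days from Adverse event reporting and harms, and align Table 4, Outcomes and Data collection and management with it. Reword the existing dose-day and clinic-visit questions, through the 1-month visit, to ask about any unpleasant health effect since the last report, on any day. Enter each answer in the CRF as an AE with its onset date, so that dose-day and non-dose-day events can be tabulated separately. State which visit closes the AE window.

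**Vital signs.** Tabulate by dose taken, and state that no conclusion about vital signs after 45 minutes can be drawn for doses above 8 µg. The monitoring schedule and the titration range must be reconciled by the sponsor; how is a clinical decision, and no schedule or dose is proposed here.

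**Cost.** New form wording, more AE entries to review, and an amendment submitted through the route the article already describes. No new visits are needed. The article reports two participants recruited, so at that point almost all of the sample could still have been collected under the changed forms.
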